One of the most important factors influencing the effectiveness of iTBS is the stimulus dose (Volz et al., 2013; Chung et al., 2016). When studying stroke patients, most researcher used a block of 600 iTBS pulses (Ackerley et al., 2014, 2016; Watanabe et al., 2018; Chen et al., 2019; Ding et al., 2021) and a few used two blocks of 600 pulses iTBS (Hsu et al., 2013; Chen et al., 2021). Previous studies in healthy human subjects suggested that iTBS might dose-dependently modulate neural plasticity, i.e., the higher the dose of iTBS, the greater the changes in neural plasticity induced (Nettekoven et al., 2014; Yu et al., 2020). Nettekoven et al. (2014) applied three blocks of 600 pulses iTBS to motor cortex and found that the cortical excitability enhancement effect was significantly greater than two blocks of 600 pulses iTBS and one block of 600 pulses iTBS. They also found that functional connectivity between M1 and ipsilateral dorsal premotor cortex continued to increase in a dose-dependent manner after 1,800 pulses of iTBS over M1. However, studies in healthy human subjects are insufficient to support the clinical application of iTBS. Other studies revealed that in patients with neurological disorders, high doses of rTMS produced stronger and longer lasting therapeutic responses than low doses (Nyffeler et al., 2009; Williams et al., 2018), but an agreement on how to select the best dose of iTBS for stroke patients with upper limb motor dysfunction is limited until now. There is a lack of studies comparing the difference in efficacy of different doses of iTBS for upper limb motor dysfunction in stroke patients.

Therefore, the objectives of this randomized controlled clinical trial are: (1) to investigate the safety and efficacy of one block of iTBS (600 pulses-iTBS), two blocks of iTBS (1,200 pulses-iTBS), or three blocks of iTBS (1,800 pulses-iTBS) in the treatment of upper limb motor dysfunction in stroke patients; (2) to compare the efficacy of three doses of iTBS; (3) to explore the neural mechanism of upper limb motor recovery after stroke using resting-state functional magnetic resonance imaging (rs-fMRI). Our hypothesis is that the higher the dose of iTBS, the greater the improvement in upper limb motor function in stroke patients. This study may provide new insights into the efficacy and underlying neuroplastic mechanisms of iTBS for treating poststroke upper limb motor dysfunction.

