### Study design

2.1.

This is a prospective, single-center, randomized, parallel, sham-controlled clinical trial. This study will be conducted at Beijing Bo’ai Hospital, China Rehabilitation Research Center (Beijing, China). Hospitalized patients will be screened in accordance with strict inclusion and exclusion criteria. After written informed consent is obtained, demographic information collection and baseline assessments are scheduled for each patient. All participants will be randomly assigned with a ratio of 1:1:1:1 to one of the following four groups: Group A, Group B, Group C, and Group D. Details of the study design and data collection are presented in Figure 1 and Table 1. Behavioral assessments will be performed at baseline (T0), at the end of the iTBS intervention (T1), and 3 weeks post-treatment (T2) to assess upper limb motor function, activities of daily living (ADLs) performance, and quality of life. In addition, rs-fMRI data will be collected before and after the end of the intervention. This study has been approved by the Medical Ethics Committee of China Rehabilitation Research Center (No.: 2022-149-01) and registered on www.chictr.org.cn under the registration number ChiCTR2300068177.

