### Outcome measures

2.6.

The Fugl-Meyer Assessment of the Upper Extremity (FMA-UE) score from baseline (T0) to end of intervention (T1) is defined as the primary outcome. The FMA-UE is a standardized scale of upper limb motor impairment ranging from 0 to a maximum of 66 points (Fugl-Meyer et al., 1975; Chen Y. F. et al., 2022). Secondary outcomes are the Wolf Motor Function Test (WMFT), Grip Strength (GS), MAS, Modified Barthel Index (MBI), and Stroke Impact Scale (SIS). The WMFT consists of 15 tasks, each of which must be completed in at least 120 s, and the performance on each task is scored on a six-point scale (0–5) (Morris et al., 2001; Wolf et al., 2001). The GS is measured with a grip dynamometer. During the measurement, the patient’s shoulder joint is abducted to 90°, the elbow joint is flexed to 90°, and the forearm is placed on the table. The patient is instructed to hold the grip dynamometer as hard as possible (Bertrand et al., 2015). The grip dynamometer automatically records the highest value. A total of 3 measurements are taken with a 1-min rest interval between each measurement. The MAS is commonly used to assess spasticity. The MAS scores for the shoulder, elbow, wrist, and fingers of the affected upper extremity will be recorded. The MBI is used to assess the patient’s ability to perform activities of daily living (ADL), including 10 items out of 100 points (Ohura et al., 2017). The SIS is one of the commonly used scales to evaluate the quality of life of stroke patients, which consists of eight items, and each item has a full score of 100 points (Mulder and Nijland, 2016), and we will take the average score of the eight items as the outcome. Each participant will undergo the following clinical assessments pre-treatment (T0), post-treatment (T1), and at the 3-weeks follow-up (T2): FMA-UE, MBI, SIS. The following clinical assessments will be performed only before and after treatment: WMFT, GS, MAS. We will also perform exploratory analyses based on the rs-fMRI data collected before and after the treatment.

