### Data analysis

2.7.

We will use SPSS version 25 for statistical analysis. Analysis of variance (continuous and ordinal data) or χ^2^ tests (categorical data) will be used to compare demographic and baseline characteristics. A mixed-design ANOVA (between-subjects factor: group; within-subjects factor: time; and time-by-group interaction) will be used to detect any significant differences in the change of outcomes. Any factor with a significant difference between the groups at the baseline will be included as a covariate in the ANOVAs. If a significant time-by-group interaction effect is found, comparisons using pairwise *t*-tests will be performed by separately comparing the changes from baseline. Bonferroni correction is applied for *post hoc* tests. Before entering the data into the ANOVAs, the Shapiro–Wilk test will be used to test whether the data are normally distributed. For non-normally distributed measures, the non-parametric Kruskal-Wallis H test is performed to compare across conditions. The level of significance is defined as *p* < 0.05 (2-tailed). For missing data, intention-to-treat (ITT) analysis is used (Matilde Sanchez and Chen, 2006).

The pre-processing of the MRI data will be in accordance with the previously described pipeline (Yeo et al., 2011). After preprocessing, regional homogeneity (ReHo), degree centrality (DC), amplitude of low frequency fluctuations (ALFF), and seed-to-voxel analyses will be performed to measure functional connectivity within motor networks. ReHo is calculated based on the Kendall’s concordance coefficient, which is used to measure the time-series synchronization between a given voxel and neighboring voxels, with higher values representing better concordance between the local voxel and the regional brain activities. In network analysis, DC is the most direct measure of node centrality. A higher degree of a node means that the node has a higher DC and the node is more important in the network. The ALFF value is related to the strength of local neural activity. It is often used to measure the BOLD signal in the frequency range of 0.01–0.1 Hz (Zang et al., 2004). Differences between conditions are considered significant if *p* < 0.05 at the voxel level. A false discovery rate (FDR) cluster corrected *p* < 0.05 is applied.

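### Single-step Bonferroni on the pairwise comparisons is valid but needlessly conservative; Holm's step-down would find slightly more at the same 5% family-wise level

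*Protocol article*

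**What the plan says.** The Study design section sets up four arms: "All participants will be randomly assigned with a ratio of 1:1:1:1 to one of the following four groups". The second objective in the Introduction is "to compare the efficacy of three doses of iTBS".

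The Data analysis section plans a mixed-design ANOVA and then a conditional step: "If a significant time-by-group interaction effect is found, comparisons using pairwise" t-"tests will be performed by separately comparing the changes from baseline". For that step, "Bonferroni correction is applied for" the post hoc tests, at a two-sided level of 0.05. The size of the Bonferroni family is not stated.

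The Outcome measures section gives two visit schedules. For three scales: "Each participant will undergo the following clinical assessments pre-treatment (T0), post-treatment (T1), and at the 3-weeks follow-up (T2): FMA-UE, MBI, SIS". For the others: "The following clinical assessments will be performed only before and after treatment: WMFT, GS, MAS". The primary outcome is FMA-UE from T0 to T1.

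**The concern.** Three of the six pairs compare an active dose with sham and three compare doses with each other, so the post hoc step is where the first two objectives are answered. It rests on 14 patients per arm, or about 11 after the planned dropout.

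Single-step Bonferroni holds every pair at 0.05/6 = 0.0083, even after some pairs have been rejected. Once a pair has been correctly rejected, fewer null hypotheses can still be true, and the same strictness for the rest is not needed to hold 5%. What is at stake is a little power in the comparisons where the trial has least.

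**Working it through.** **Inputs.** From the article: four arms 1:1:1:1, alpha 0.05 two-sided, 44 patients before dropout, 20% dropout, 14 per arm, planning effects d = 0.6 and f = 0.3. Assumed: a family of six T0-T1 pairs, normal data with equal variances, effects in SD of change, and a correlation of 0.5 between visits where three visits are modelled.

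**The plan's own figure.** The article gives no error rate for the post hoc step, but its sample size can be reproduced. For a repeated-measures interaction with four groups, three time points and correlation 0.5, lambda = f² × N × m/(1 − rho) = 0.09 × 44 × 3/0.5 = 23.76 on 6 and 80 df, giving power 0.961 at N = 44. Then 11/(1 − 0.2) = 13.75, so 14 per arm and 56 in total. This fits an interaction test that spans T0, T1 and T2.

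**Why Bonferroni falls below 5%.** If m0 of the six nulls are true, its error is at most m0 × 0.05/6. Simulated values are for the gate on T0-T1 change, with separate t-tests and 11 or 14 per arm.

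| True pattern | m0 | Bound | Gate + Bonferroni | Gate + Holm |
|---|---|---|---|---|
| All four equal | 6 | 5.0% | 3.0-3.3% | the same |
| Three equal | 3 | 2.5% | 2.2-2.3% | 4.4% |
| Two equal pairs | 2 | 1.7% | 1.6% | 4.8-4.9% |
| One equal pair | 1 | 0.8% | 0.8% | 4.9% |

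For FMA-UE the interaction covers three visits. Bonferroni's error for the T1 pairs is then 1.8-1.9% with no effect, 2.1-2.4% with three arms equal, and 4.1% when arms differ only at T2. Over both gates the range is about 1-4%.

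**Why Holm is safe.** Holm orders the six p-values and compares them with 0.05/6, 0.05/5, 0.05/4, 0.05/3, 0.05/2 and 0.05, stopping at the first failure. When the first true null is reached, at least m0 hypotheses remain, so its threshold is at most 0.05/m0, and m0 × 0.05/m0 = 5%. A gate can only remove rejections, so the bound holds with or without it. Every Holm threshold is at least 0.05/6, so nothing that Bonferroni rejects is lost.

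**Size of the gain.** 14 per arm; means in the order sham/600/1,200/1,800; gate on T0-T1 change. Repeat runs differ by about 0.01.

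| Assumed means | True differences found, Bonferroni | Holm | Relative gain |
|---|---|---|---|
| 0/0/1/1 | 1.73 | 1.92 | 1.92/1.73 = 1.11 |
| 0/0.4/0.8/1.2 | 1.27 | 1.39 | 1.39/1.27 = 1.09 |
| 0/0.2/0.4/0.6 | 0.25 | 0.27 | 0.27/0.25 = 1.08 |

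Detection of 1,800 pulses versus sham moves from 43% to 48% under 0/0/1/1, and from 11.2% to 11.6% under 0/0.2/0.4/0.6. With the three-visit gate and equal effects at T1 and T2, the second and third rows become 1.24 to 1.36 and 0.21 to 0.23. With 11 per arm under that gate they are 0.88 to 0.96 and 0.15 to 0.16. The chance of at least one rejection is the same for both methods, because both start at 0.05/6.

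**The case against.** The strongest reply is that Bonferroni after an omnibus test is standard and valid, that the article contradicts nothing, and that the gain is negligible where the trial was planned. Much of this stands. With the top dose at d = 0.6, Holm adds about half a percentage point for 1,800 pulses versus sham, and power is low under either method. The clearer gains need effects of 1.0-1.2 SD, about twice the planning value. What does not follow is that the change is mere taste: for decisions at the same family-wise level, Holm is never worse.

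The family of six is also an assumption. Comparing changes from baseline could take in T2. If T1 and T2 were each corrected with 0.05/6, joint error was mostly 3.2-4.3% but reached 6.1% in one configuration, so the conservatism described here belongs to the six T0-T1 pairs only.

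A reader might infer that the gate and Bonferroni correct the same multiplicity twice. They do not. With four arms the gate protects only against the complete null. Gate plus uncorrected t-tests gives 12% error with three equal arms and 10% with two equal pairs, so a pairwise correction is still needed. With three equal arms Bonferroni's error is 2.2-2.3% with or without the gate.

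A reader might also want Shaffer steps starting at 0.05/3, on the ground that a rejected interaction leaves at most three true pairwise nulls. That holds only if the gate tests the same T0-T1 change. For FMA-UE, MBI and SIS the interaction spans three visits and can open on T2 alone; T1 family-wise error was then 7.5-8.0%.

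**Conclusion.** The point holds as a small gain in efficiency, not as an error. Single-step Bonferroni is valid and mildly wasteful. For six T0-T1 pairs its family-wise error is about 1-4%, and Holm turns the unused part into roughly 8-11% more true differences found in the patterns examined, without changing the chance of any finding. It would be tempting to say that the plan spends only 2-3% of its error, but that is not a general figure: simulated values run from 0.8% to just above 4%, depending on the true means and the gate. The conclusion rests on the assumed six-pair family, normal data with equal variances, and correlation 0.5 for the three-visit case. The ordering of the two methods does not depend on these assumptions; the size of the gain does.

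**What to change.** In Data analysis, replace the Bonferroni sentence with one stating that Holm's step-down will be applied to the six pairwise between-arm comparisons of T0-T1 change, and name those six pairs as the family. Leave the omnibus test as it is. Keep Holm's first step at 0.05/6, and do not use Shaffer steps starting at 0.05/3 for FMA-UE, MBI or SIS.

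The cost is one sentence and ordering six p-values; no extra patients or data are needed. The real loss is that Holm gives no simple simultaneous confidence intervals. Unadjusted 95% intervals can be shown if labelled as unadjusted, because such an interval may exclude zero while the Holm-adjusted p-value is not significant.

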#### Inclusion criteria

2.2.1.

Participants are considered eligible if they meet the following criteria: (1) have a unilateral ischemic or hemorrhagic subcortical stroke; (2) first or previous stroke without residual disability (modified Rankin Scale ≤1 before this onset); (3) 1–6 months post-stroke; (4) are 35–75 years old; (5) presented with a unilateral upper limb motor dysfunction with a Brunnstrom stage score between 2 and 5 in the upper limb or hand; (6) can sign an informed consent form.

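### A Shapiro-Wilk pre-test chooses the primary FMA-UE analysis from the data, and its Kruskal-Wallis fallback falls outside the plan's time factor, covariate rule and pairwise step

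*Protocol article*

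**What the plan says.** All references are to the protocol article.

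- **Primary outcome** (Outcome measures, 2.6). The FMA-UE "score from baseline (T0) to end of intervention (T1) is defined as the primary outcome". The scale measures "upper limb motor impairment ranging from 0 to a maximum of 66 points".
- **Entry range** (Inclusion criteria, 2.2.1). Patients need a "Brunnstrom stage score between 2 and 5 in the upper limb or hand".
- **Planned model** (Data analysis, 2.7). "A mixed-design ANOVA (between-subjects factor: group; within-subjects factor: time; and time-by-group interaction) will be used" for changes in the outcomes. Factors that differ significantly between groups at baseline become covariates, and this rule is written for the ANOVAs. Bonferroni-corrected pairwise t-tests on change from baseline follow only if the interaction is significant.
- **Pre-test** (2.7). "Before entering the data into the ANOVAs, the Shapiro–Wilk test will be used to test whether the data are normally distributed".
- **Fallback** (2.7). "For non-normally distributed measures, the non-parametric Kruskal-Wallis H test is performed to compare across conditions". No outcome is exempt. The variable to be ranked, T1 score or change, is not named.

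**The concern.** The rule makes the primary test depend on a preliminary test of the same data, and it does so badly in two ways.

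First, it is aimed at the wrong quantity if read literally. The T0-T1 interaction in a mixed ANOVA is the same test as a between-group comparison of change, so what should be roughly normal is the residual of the change. Raw FMA-UE scores can be flat or skewed simply because patients of very different severity enter on a bounded scale, while the changes behave well.

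Second, the fallback does not fit the rest of the section. Kruskal-Wallis takes one value per patient, so it contains neither time nor an interaction. The covariate rule does not reach it. The pairwise comparisons, which serve the objective of comparing the three doses, wait for a significant interaction that the fallback cannot produce. At stake are the power of the primary comparison and a choice of variable that might be made with the data in hand.

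**Working it through.** **1. The plan's own figure.** Sample size (2.3) gives 44 evaluable patients for f = 0.3, alpha 0.05 and power 0.95. Using the noncentral F for a within-between interaction, λ = f²·N·m/(1−ρ), with df (k−1)(m−1) and (N−k)(m−1), k = 4, and assuming ρ = 0.5 and sphericity:

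- m = 3 time points: λ = 0.09 × 44 × 3 / 0.5 = 23.76, df 6 and 80, power 0.96. This reproduces 44.
- m = 2 (T0 and T1): λ = 15.84, df 3 and 40, power 0.90.
- One-way comparison of a single value per patient: λ = 0.09 × 44 = 3.96, df 3 and 40, power 0.32.

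The 44 therefore rests on a repeated-measures interaction. It does not cover a rank test at one time point.

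**2. How often would the rule switch?** The article gives no mean, SD or shape for FMA-UE, so every shape here is an assumption. Except where the table says otherwise, Shapiro-Wilk is run at 0.05 on pooled raw scores, and the range is for 44 to 56 patients.

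| Assumed shape and what is tested | Chance of rejection |
|---|---|
| Flat baseline (6 to 58), T0 or T1 fails | about 70% to 86% |
| Skewed baseline, T0 or T1 fails | 79% to 91% |
| U-shaped, one time point | 86% to 96% |
| Milder skew, one time point | 47% to 63% |
| Near-normal or truncated-normal baseline, T0 or T1 fails | about 8% to 14% |
| Flat baseline, N = 44, T1 only | 20% |
| Flat baseline, N = 44, pooled change | 6% |
| Flat baseline, N = 44, residuals of change | 5% (the nominal rate) |

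With a flat baseline the switch is thus driven by the spread of severity at entry, not by any failure of the model's assumption.

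**3. What does the switch cost?** Assumed: flat baseline 6 to 58, mean gains of 0/2/4/6 points, change SD 6, N = 44.

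- Baseline variance = 52²/12 = 225.3. T1 variance within groups = 225.3 + 36 = 261.3. Correlation = √(225.3/261.3) ≈ 0.93 within groups, or about 0.92 once the spread of group gains (variance 5) is added.
- ANOVA on change: λ = 44 × 5/36 = 6.11, power 0.48. Simulation gives 47% to 48%.
- ANOVA on T1 alone: λ = 44 × 5/261.3 = 0.84, power 0.10. Simulation gives 9.7%.
- Kruskal-Wallis by simulation: about 8% on T1, about 45% on change.

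Power under the whole rule is roughly P(switch) × fallback power + P(no switch) × ANOVA power:

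- T1 fallback: 0.70 × 0.08 + 0.30 × 0.47 = 0.197, about **20%**.
- Change fallback: 0.70 × 0.45 + 0.30 × 0.47 = 0.456; direct simulation gives about **45%**.
- No switch, ANOVA on change always: about **47%**.

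At N = 56 with a T1 fallback, simulated power is about 19% against 60% for always testing the interaction, because a larger sample triggers the pre-test more often.

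**4. Dependence on the correlation.** Assumed: 11 per group, a linear dose trend with f = 0.3 on the T1 scale, normal data.

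| T0-T1 correlation | ANOVA on change | Kruskal-Wallis, T1 | Kruskal-Wallis, change |
|---|---|---|---|
| 0.5 | 0.32 | 0.30 | 0.29 |
| 0.7 | 0.52 | 0.30 | 0.48 |
| 0.8 | 0.71 | 0.29 | 0.67 |
| 0.9 | 0.96 | 0.30 | 0.94 |

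With right-skewed data, Kruskal-Wallis on change does slightly better than ANOVA on change (0.38/0.58/0.76/0.96 against 0.32/0.51/0.68/0.93). On T1 it stays near 0.45, which is a gain at correlation 0.5.

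The type I error of the two-stage rule was not computed.

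**The case against.** The strongest reply is that the section can be read more kindly. It speaks of changes in outcomes and of comparing changes from baseline, and the primary outcome runs from T0 to T1. If Shapiro-Wilk is applied to changes, the switch is uncommon even with a flat baseline (6% pooled, 21% if any one of the four groups may trigger it). If Kruskal-Wallis is also run on change, it tests the T0-T1 contrast by ranks, accounts for baseline and costs almost nothing. The article condenses a fuller plan, which may settle which values are tested and what happens when T0 fails and T1 passes.

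Much of this stands. The missing operational detail is not counted as a defect here. Three stronger conclusions that a reader might draw are not supported:

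- *That the switch is likely for FMA-UE.* The 0-66 scale and the Brunnstrom range make non-normal raw scores plausible, but no distribution is given.
- *That the fallback discards the baseline.* The text names no variable; it neither prescribes nor excludes change.
- *That power falls to 8%.* That figure needs the T1 score, a correlation near 0.92 and a switch every time. Ordinary ANOVA on T1 does hardly better (9.7%), so the loss comes from ignoring baseline, not from ranking.

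The reply does not remove the rule itself. A data-driven switch of the primary test is written into the plan. Even on the kindest reading, the covariate rule and the pairwise trigger do not carry over to the fallback.

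**Conclusion.** The point holds as a defect of a stated rule: the primary FMA-UE test is selected by a normality test on the data, and the fallback does not connect to the interaction, the covariates or the dose comparisons. Its practical size cannot be fixed from the article. It ranges from a loss of about 2 percentage points of power (45% against 47%, change fallback) to about 27 points (20% against 47%, T1 fallback) in the flat-baseline scenario with 44 patients. It is small if the baseline is near normal, and it shrinks at lower T0-T1 correlations. The baseline shape, gains, change SD and correlation are all assumptions. That so much turns on choices the rule does not state is reason enough to change it. It should be corrected before unblinding, but it does not invalidate the design.

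**What to change.** For FMA-UE, delete the Shapiro-Wilk switch and fix one primary analysis in advance that uses the T0 score whatever the distribution looks like. Either the T0-T1 time-by-group interaction already planned or T1 with T0 as covariate would serve. The second would be a new choice, since the plan now adds covariates only when groups differ at baseline. Examine model residuals as a diagnostic only. Name one sensitivity analysis, rank-based or by permutation, on change or on baseline-adjusted scores, and state its variable and how its pairwise dose comparisons are made.

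Cost: a few sentences in the analysis section and one sensitivity run. No extra patients, visits or measurements are needed.

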## Discussion

3.

This randomized controlled clinical trial aims to investigate and compare the efficacy of three doses of iTBS on the recovery of upper limb motor function in stroke patients. Furthermore, we hope to provide a theoretical basis for clinical application by investigating the neural effects of iTBS intervention on upper limb motor dysfunction. Our results may provide supportive evidence for the optimal dose of excitatory iTBS intervention in the treatment of upper limb motor dysfunction after stroke.

In this study, we hypothesize that iTBS can promote upper limb motor recovery in stroke patients by modulating functional connectivity within the motor network. We also hypothesize that the higher the stimulus dose, the greater the improvement in motor function. The following evidence supports this hypothesis. Increasingly, it is thought that increasing the dose of rehabilitation may lead to better motor function outcomes in stroke patients (Cooke et al., 2010; Lang et al., 2015; Winstein et al., 2019). rTMS is an important physiotherapeutic approach, and its use in rehabilitation is inseparable from the choice of parameters, with the stimulus dose being of particular importance. and rTMS has gained attention in recent years as a promising physical therapy approach. iTBS is a type of rTMS that has great potential in the treatment of post-stroke motor dysfunction and has attracted much attention in recent years. Previous studies on healthy subjects have found that iTBS with more stimulus pulses more significantly enhances motor cortex excitability and functional connectivity within the motor network. However, studies comparing the effects of different doses of iTBS on upper limb motor recovery in stroke patients are lacking, and our study will fill this gap.

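### Section 2.7 presents ALFF and ReHo as measures of functional connectivity, but its own definitions make them local measures, so a change in either alone could be reported as support for the connectivity mechanism

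*Protocol article*

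**What the plan says.** Section 2.7 (Data analysis) of the protocol article gives one purpose to four analyses. It lists ReHo, DC and ALFF, and the sentence ends: "seed-to-voxel analyses will be performed to measure functional connectivity within motor networks". It then describes three of them one by one:

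- ReHo is "used to measure the time-series synchronization between a given voxel and neighboring voxels".
- On DC: "A higher degree of a node means that the node has a higher DC and the node is more important in the network".
- On ALFF: "The ALFF value is related to the strength of local neural activity".

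Section 3 (Discussion) states the mechanism that the imaging is meant to inform: "iTBS can promote upper limb motor recovery in stroke patients by modulating functional connectivity within the motor network". Section 2.6 (Outcome measures) gives the standing of the imaging work: "We will also perform exploratory analyses based on the rs-fMRI data collected before and after the treatment". Section 2.7 sets a voxel-level and a cluster-level significance threshold for the imaging. It does not say which of the four measures bears on the connectivity hypothesis.

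**The concern.** The purpose given to ALFF and ReHo does not match what the next sentences say they measure. The hypothesis concerns connectivity within a network, that is, coupling between regions. A measure of one location's signal strength, or of agreement among adjacent voxels, does not use the signal of another motor region.

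At stake is the mechanistic conclusion. If the only group difference appeared in an ALFF or ReHo map, the sentence in section 2.7 would allow the authors to present it as evidence that iTBS changed functional connectivity in the motor network. That attribution would be unsupported, because nothing in such a map shows that two motor regions became more or less coupled.

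**Working it through.** The plan gives no figure to reproduce here. The check sets the text side by side and then illustrates it.

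**1. Stated purpose against stated definition (section 2.7)**

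| Measure | Purpose given | What the paragraph says it measures | Fit |
|---|---|---|---|
| ALFF | functional connectivity | local signal strength | none: no relation between voxels |
| ReHo | functional connectivity | synchrony with adjacent voxels | short-range only |
| DC | functional connectivity | a node's importance in the network | network measure |
| Seed-to-voxel | functional connectivity | not described further | between-region measure |

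**2. The article's own usage.** The Introduction describes the motivating result in healthy subjects as connectivity between M1 and the dorsal premotor cortex, which is a relation between two regions. The Discussion names cortical excitability and network connectivity as two things, and elsewhere names network activity and connectivity separately. Treating a local activity measure as connectivity departs from that usage.

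**3. Illustration.** Inputs from the article: runs of 8 min 6 s with TR 2 s, so 486 / 2 = 243 volumes; band 0.01–0.1 Hz. Assumptions: a 27-voxel neighbourhood in each of two regions; a shared regional signal of SD 1 plus independent voxel noise of SD 0.7; a correlation of 0.4 between the two regional signals; 300 replicates. One property is changed at a time. ReHo is Kendall's coefficient, and the seed measure is the correlation between the two regional means.

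| Scenario | ALFF | ReHo | Seed correlation |
|---|---|---|---|
| Baseline | 1.076 | 0.663 | 0.390 |
| Local amplitude × 1.5 | 1.624 | 0.662 | 0.390 |
| Local synchrony raised (noise SD 0.7 to 0.4) | 0.953 | 0.852 | 0.392 |
| Between-region correlation 0.4 to 0.7 | 1.078 | 0.665 | 0.687 |

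- Amplitude: 1.624 / 1.076 = 1.51, so ALFF rises 51% while the seed correlation does not move.
- Synchrony: 0.852 / 0.663 = 1.29, so ReHo rises 29% while the seed correlation is essentially unchanged.
- Coupling: ALFF and ReHo stay flat, and the seed measure rises from 0.390 to 0.687.

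ALFF and ReHo can therefore change when coupling between regions does not. The last row also shows that the seed-based analysis, which is planned, picks up a change in coupling.

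**The case against.** Several counter-arguments have force.

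- **The definitions already correct the sentence.** The text after the list describes ALFF and ReHo accurately, so the problem may be no more than a loose umbrella clause. This stands in part. The definitions are right, but the purpose clause still contradicts them, and it is the purpose clause that links the measures to the hypothesis. A fuller analysis plan might rank the measures, but it would not make the published sentence correct.
- **The imaging is exploratory.** Section 2.6 says so, and an exploratory aim need not name a single deciding measure. This stands and limits the severity. It does not make the label right.
- **ReHo and DC are not clearly mislabelled.** ReHo is synchrony between voxels and can be read as short-range connectivity; DC is a network measure. This stands. The contradiction is clear for ALFF, weaker for ReHo, and not made against DC.
- **The illustration is close to algebra.** Multiplying a whole time series by a constant must raise ALFF and leave a correlation alone. If only the shared signal grew, the measures would move together. Take the shared signal as half of voxel variance and its correlation with the remote region as 0.3, and scale the shared signal by 1.3. The shared variance becomes 0.5 × 1.69 = 0.845, and the voxel-level correlation goes from 0.3 × √0.5 = 0.212 to 0.3 × √(0.845 / 1.345) = 0.238, about 12% higher. The within-region correlation behind ReHo goes from 0.50 to 0.845 / 1.345 = 0.63. This stands: the measures can move apart but need not. The point needs only that they can.

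A reader might infer that a real connectivity change would be missed. The documents do not support that, because seed-to-voxel analysis and DC are planned in the same sentence. A reader might also infer that a local change will be counted as a connectivity change. No scoring or decision rule says so; the wording only permits such a report.

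**Conclusion.** The point holds as a minor one. Section 2.7 assigns ALFF and ReHo a purpose that its own definitions contradict: ALFF does not measure connectivity, and ReHo is at most short-range synchrony. The possible harm is a false mechanistic attribution within an exploratory aim, should a difference appear in either measure alone. The primary outcome (FMA-UE), the sample size and the error control of the primary analysis are unaffected.

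The conclusion rests on the article's definitions and on reading connectivity within the motor network as coupling between its regions, which is how the article uses the term elsewhere. The simulated figures depend on assumed signal, noise and correlation sizes. They show that the measures can separate, not how far they would separate in these patients.

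**What to change.** Reword section 2.7, and carry the wording into the analysis plan:

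1. Report ALFF as local activity and ReHo as local synchrony.
2. Tie the functional-connectivity hypothesis to the between-region measures already planned: seed-to-voxel analysis within the motor network, supported by DC.
3. State that a difference in ALFF or ReHo alone does not support the connectivity claim.

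This needs no new scans, patients or procedures. The cost is that a positive ALFF or ReHo map on its own no longer counts towards the connectivity hypothesis, though it can still be reported as a finding about local activity or synchrony.
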